**Figure 1 F1:**
[figure not shown]
Ipsative feedback pieces of fruit and vegetable consumption.

### Measurement instruments

If not mentioned otherwise, all items will be measured with the use of visual analogue scales (VAS). These scales have several advantages in comparison with Likert-scales: participants need less explanation to answer question, nuancing of responses is more exactly, drop-out rates are lower in and VAS allows for grater statistical analysis [60,61].

### Demographic and socioeconomic characteristics

Several items address the demographic and socioeconomic characteristics. These include gender, age, level of education, family status, living conditions, country of origin, native language and employment status.

### Health status

Health status will be measured by asking the reasons for the cardiac rehabilitation, body height and body weight.

### Past health behavior

The level of physical activity will be assessed with the use of the short version of the International Physical Activity Questionnaire (IPAQ) [62]. Participants will be asked to estimate how many days during the past seven day they were vigorous and moderate physically active. Further, the amount of days and spend time for walking during the past seven days will be asked. The IPAQ is a valid measurement instrument which allows an international comparison of participant’s physical activity level.

To assess the fruit and vegetable consumption during the past seven days, four items will be used. Participants will be asked to count the number of consumed portions or glasses fruit and vegetable a day. It will be distinguished between fruit, fruit juice/vegetable juice, cooked or steamed vegetable, and salad and raw vegetable [63].

### Intention

Intention to perform physical activity will be measured with the use of three items on a VAS scale ranging from *not true* to *exactly true*. These items are: “*On 5 days a week for 30 minutes (or a minimum of 2.5 hours per week), I have the intention to …” “…perform strenuous physical activity (heart beats faster, sweating)”. “…be moderately physically active (not fatiguing, mild sweating)*” and “…*be moderately physically active (not fatiguing, mild sweating)*” [64].

Intention about fruit and vegetable consumption will also be measured with three items: *“I seriously intent to …” “… eat at least 5 portions of fruit and vegetable daily “, “…eat fruit and vegetable at every meal” and “drink at least one fruit or vegetable juice every day*” [64].

### Stages of change

The stage of change for physical activity will be assessed with the item: *“Please think about your typical weeks: Did you engage in physical activity at least 5 days per week for at least 30 minutes?” *[64]. Regarding dietary behavior, participants will be asked *“Please think about what you have typically consumed during the last weeks: Did you eat five portions of fruit and vegetables per day?”* Responses are based on a rating scale with verbal anchors *“No, and I do not intend to start”*; “*No, but I am considering it”*; *“No, but I seriously intend to start”*; *“Yes, but only for a brief period of time*”; *“Yes, and for a long period of time”*.

### Self-efficacy

The concept of self-efficacy will be measured in three parts; motivational self-efficacy refers to one’s confidence to perform a specific behavior. Maintenance self-efficacy refers to one’s confidence to perform a specific behavior over a long period of time and recovery self-efficacy refers to one’s confidence to resume a specific behavior after a discontinuation [52].

Motivational self-efficacy will be assessed with one item for physical activity: *“I am certain that I can be physical active a minimum of 5 days a week for 30 minutes even it is difficult.”* And also with one item for fruit and vegetable consumption: *“I am certain that I can eat at least 5 portions of fruit and vegetables a day even if it is difficult”*[65].

Maintenance self-efficacy will be assessed with two items for each target behavior. *“I am certain that I can be physically active permanently at a minimum of 5 days a week for 30 minutes …* / *“I am certain that I can permanently eat 5 portions of fruit and vegetable a day…” “… even if it takes a lot of time till I am used to do it”* and *“… even if I have worries and problems”*[66].

Recovery self-efficacy will be measured with two items for each behavior: *“I am certain that I can again be physically active a minimum of 5 days a week for 30 minutes / I am certain that I can again eat 5 portions of fruit and vegetables a day …” “even if I changed my concrete plans several times”* and *“… even if I skipped a few times”*[66]. Participants can answer all self-efficacy items on a VAS-scale ranging from *don’t agree at all* to *agree completely*.

### Outcome expectancies

Participants’ outcome expectancies will be measured by four items; two about positive and two about negative expectancies. *“If I am physical active 5 days a week for at least 30 minutes, then… ”… this is good for my health”*, *”…I feel better afterwards”*, *”…it will cost me a lot of time”* and *“…this will be a financial burden”* . The items for fruit and vegetable consumption: *“If I daily eat 5 portions of fruit and vegetable, then…” “… this is good for my health”*, *“…I feel better afterwards”*, *“…it will cost me a lot of time”* and *“…this will be a financial burden”*[67]. Answers ranging from *don’t agree at all* to *agree completely*.

Also outcome expectations regarding fruit and vegetable consumption will be assessed with six items: “If I consume at least 5 portions of fruit and vegetable a day, then …” “… this good for my health”, *“…I feel better afterwards”, “… I get more energy”, “…it will cost me a lot of time”*, *“…this will be a financial burden”* and *“… this will cost a lot of effort”. Answers can be given on a* VAS-scale (*totally disagree* to *totally agree).*

### Risk perception

To assess participants risk perception an adaption of Perloff’s and Fetzer’s [68] perceived vulnerability scale will be used: *“How likely is it that you will have a sometime in your life …” “… a high cholesterol level?”*, *“… a heart attack?”*, “…*a high blood pressure?”*, *“… a stroke?”* and *“… a cardiovascular disease?”*. Answers can be given on a VAS-scale: *unlikely to very likely*.

### Action plans

Action planning will be assessed with the use of three items for physical activity and with three items for fruit and vegetable consumption. For both target behaviors the question starts with: “*For the next month I already planned in detail …” “… which physical activities I would like to do.” “… where I will be physical active” and“… on which days I will be physical active”*[69].

Fruit and vegetable consumption will start with the same beginning following with these three items: *“…when I will eat 5 portions fruit and vegetable”, “which fruit and vegetable I will eat”,* and *“… how I will prepare the food”*. Participants can agree or disagree on a VAS-scale [69].

### Coping plans

If and to what degree participants have made coping plans will be measured with three items for each of the two target behaviors. Physical activity: “*For the next month I already planned in detail …” “… when I have to be especially cautious not to stop being active”, “… what I can do in difficult situations to stick to my intentions”* and “*… how I continue to stay active even when something comes in between”*. Fruit and vegetable consumption will have the following items *“… when I need to be especially cautious not to fall into my old eating habits”, “… what I can do in difficult situations to stick to my intentions”* and “*… how I continue to eat healthy even when something comes in between”*. Answers can be given on a VAS-scale (*don’t agree at all* to *agree completely*) [69].

### Social support

Perceived social support will be assessed with three items for each behavior [70,71]. For physical activity the items are: “My partner helps me/My family helps me/My circle of friends and acquaintances help me… to be me to be physical active for at least 30 min. on 5 days a week (or a minimum of 2.5 hrs. per week)”. Perceived social support for fruit and vegetable consumption will be assessed with: “My partner helps me/My family helps me/My circle of friends and acquaintances help me… to eat 5 portions of fruit and vegetable per day”.

### Habit

The habituation of physical activity and fruit and vegetable consumption will be measured with an abbreviated version of the Self Report Habit Index (SRHI) [72]. *“Being physically active for at least 30 minutes on 5 days a week is something that…”* and *“Eating 5 portions of fruit and vegetable per day is something …” “… has become a confirmed habit”* and *“… I do without thinking about it”*. Answer can be given on a VAS-scale ranging from *do not agree* to *completely agree*.

### Quality of life

Quality of life will be determined by means of the World Health Organization Quality of Life-BREF (WHOQoL-BREF) questionnaire [73,74]. This instrument was developed to assess quality of life in a cross-culturally comparable way. General quality of life will be measured via the question: “How would you rate your quality of life?” with an answer category from *very poor* to *very good*. The physical health subdomain with seven items will also be used. Examples of the physical health items are: “To what extent do you feel that physical pain prevents you from doing what you need to do?”, “How much do you need any medical treatment to function in your daily life?” and “How satisfied are you with your ability to perform your daily living activities?”

### Depression

The level of depression will be measured using the Center for Epidemiologic Studies Short Depression Scale (CES-D 10) [75]. The ten items from this scale are: In the past week … “*I was bothered by things that usually don’t bother me“, “I had trouble keeping my mind on what I was doing”, “I felt depressed”, “I felt that everything I did was an effort”, “I felt hopeful about the future”, “I felt fearful”, “My sleep was restless”, “I was happy”, “I felt lonely” and “I could not get going*”. Answers can be given on a 4-point Likert scale ranging from *rarely or none of the time (less than 1 day)* to *most or all of the time (5–7 days)*.

### Subjective age

Based on Boehmer [76], two items will be asked to assess the subjective age of the respondents. *“How old do you feel physically?*” and “*How old do you feel mentally?”*

### Compensatory health beliefs

The scales used to access compensatory health beliefs concerning physical activity and fruit and vegetable consumption will be based on Knäuper and colleagues [77]. The scale contains four items such as: “*Too little physical activity can be compensated by eating less”*. Answers are indicated on a VAS-scale (*don’t agree at all* to *agree completely*).

### Main study outcomes

The primary study parameter of this study is to analyze the effectiveness of a rehabilitation aftercare program with regard to the level of physical activity and fruit and vegetable intake. The effect of the program will be compared between the intervention group and the control group as well as between the different countries. Secondary study parameters that will be investigated are self-efficacy, outcome expectations, habit, compensatory cognitions, social support, action and coping planning, intention to change, duration absence from work, quality of life and wellbeing. The other study parameters which will be considered are demographic variables, socioeconomic status, stage, age, gender, depression, and health status.

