### Power analysis

The power analysis was based on the assumption that the intervention will result in a small improvement of effect to improve fruit and vegetable consumption and in a small to medium effect to improve physical activity for the study conditions [38]. The calculation was based on an effect size of 0.3, with a power (1-β) of 0.8 and alpha of 0.05.

No cluster effect is expected due to the fact that the randomization of the participants is independent of the place of recruitment. Further, it is necessary to take interaction effects into account between the intervention and the control group, and between Germany and the Netherlands.

Therefore, to be able to detect a small to medium effect, 263 people have to participate in every group in each country. This means that the required total sample size will need to consist of 1052 participants, not adjusted for potential drop out during the intervention.

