### Statistical analysis

Descriptive statistics will be used to describe baseline characteristics of the study. We will assess whether there are significant differences between the intervention group in comparison with the control group according to physical activity and nutrition by means of linear regression analysis in PASW (SPSS). The pre-test and post-test measurements of the control group will be compared with the measurements of the intervention and controle group with regard to the target behaviours.

To be able to assess the impact of the intervention on the performance of physical activity and fruit and vegetable consumption, we intend to perform several analyses of covariance (ANCOVA) after four weeks (T3) and six months (T4), controlling for the baseline performance. Multivariate regression analysis will be used to determine possible confounding or modification effects. Regression analysis will allow us to identify the percentage of variability of the dependent variable that is explained by the determinants used. In order to detect differences between the study condition and the control group, effect sizes will be calculated for each study group separately [78].

Subgroup analyses will be performed to determine if the benefit of the intervention depends between groups like nationality or socioeconomic status [79]. Further, dose–response-analyses will be conducted with logistic regression to see if the intervention effect depended on the time spent on the webpage.

Baseline characteristics of participants who dropped out will be compared with participants who finished the intervention to examine whether drop out is at random or determined by specific characteristics.

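### Effectiveness is judged on two unranked behaviours at two time points, with one alpha of 0.05 and no primary time point or success rule

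*Protocol article*

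**What the plan says.** **Outcome.** Under Main study outcomes, the primary parameter is the programme's effectiveness "with regard to the level of physical activity and fruit and vegetable intake". The two behaviours stand side by side. Neither is ranked first, and they are not declared co-primary.

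**Tests.** Under Statistical analysis, the impact on both behaviours is assessed by several "analyses of covariance (ANCOVA) after four weeks (T3) and six months (T4), controlling for the baseline performance". Neither time point is called primary. The same section plans a linear regression for significant group differences in the same behaviours and gives no time point for it.

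**Alpha.** The only significance level in the article is in the Power analysis: "The calculation was based on an effect size of 0.3, with a power (1-β) of 0.8 and alpha of 0.05". Sidedness is not stated. That section expects a small effect on fruit and vegetable consumption and a small to medium effect on physical activity, but uses one effect size and one alpha for both.

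**Hypothesis.** The Discussion words the hypothesis jointly: the intervention group will improve on both behaviours and maintain them for longer than the control group.

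**The concern.** One question (does the programme work?) is put to at least four tests of equal standing. Nothing in the article says whether one significant result is enough, whether one behaviour at both time points is needed, or whether all four must succeed. The error rate attached to the conclusion depends on that choice, and a reader of the results could not tell which comparison was meant to be decisive.

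The time point matters for a further reason. Table 1 has the waiting-list group start the intervention after T2, and Table 2 puts the physical activity sessions in weeks 1 to 4 and the fruit and vegetable sessions in weeks 5 to 8. On that schedule, the control group at T3 would be about four weeks into the programme, and at T4 it would have had time to finish. T2, T3 and T4 are then different contrasts and may disagree. Without a named primary, the decisive one can be chosen after the data are seen.

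**Working it through.** **Inputs from the article.** Two behaviours; two ANCOVA time points; alpha 0.05; power 0.8; effect size d = 0.3; "263 people have to participate in every group in each country"; a total of 1052, "not adjusted for potential drop out during the intervention". **Assumptions.** Two-sided tests; correlations between tests; dropout rates. The article gives none of these.

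**1. The plan's own sample size.** For two means, n per group = 2(1.960 + 0.842)² / 0.3² = 174.4, so 175. The stated 263 does not follow from the stated inputs. The total does follow from 263: 4 × 263 = 1052, or 2 × 263 = 526 per arm across both countries. The section says that interaction effects must be taken into account but gives no size for them. That may explain the larger number, so failure to reproduce it does not prove it wrong. Nothing below depends on how 263 was reached.

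**2. Number of tests.** 2 behaviours × 2 time points = 4, counting the ANCOVAs only. The regression could add to this.

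**3. Error if any one of the four suffices, each at two-sided 0.05.**
- Either direction, independent tests: 1 − 0.95⁴ = 0.185. For two-sided normal tests this is a ceiling under any correlation (Šidák inequality).
- Favouring the programme only, independent tests: 1 − 0.975⁴ = 0.096, against 0.025 for a single test.
- Simulated with assumed correlations of 0.5 to 0.9 between time points and 0 to 0.5 between behaviours (1,000,000 draws per setting): 12.6% to 17.3% in either direction, and 6.3% to 8.9% in favour of the programme.

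**4. Error if all four must succeed.** At most 0.05, with no adjustment.

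**5. One time point, two behaviours.** Unadjusted, either direction, independent: 1 − 0.95² = 0.0975. Holm over the two holds this at or below 0.05.

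**6. Cost in power.** Under Holm, the least favourable case for a behaviour is testing at 0.025. By normal approximation, power = Φ(d√(n/2) − z), with z = 1.960 at 0.05 and 2.241 at 0.025.

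| Dropout (assumed) | n per arm | d | Power at 0.05 | Power at 0.025 | Loss (points) |
|---|---|---|---|---|---|
| none | 526 | 0.3 | 99.8% | 99.6% | 0.3 |
| none | 526 | 0.2 | 90.0% | 84.2% | 5.9 |
| 20% | 421 | 0.2 | 82.7% | 74.5% | 8.1 |
| 30% | 368 | 0.2 | 77.5% | 68.2% | 9.3 |
| 40% | 316 | 0.2 | 71.0% | 60.7% | 10.3 |

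Losses are taken from unrounded powers.

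**The case against.** The strongest reply is that the inflated error is not in the document. A reader might infer that each of the four tests is run at an unadjusted 0.05 and that any one of them counts as success, so that the chance of a false claim of effectiveness is 18.5% instead of 5%. The article does not support that reading, for three reasons.

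- **Unadjusted** would be an inference from silence. The 0.05 is an input to the sample size, and a multiplicity procedure may sit in an analysis plan that is not shown.
- **Any one suffices** is not stated. The Discussion's hypothesis is joint, and under a rule that all must succeed no correction is needed. Because the Power analysis gives each behaviour its own expected effect, two separate behaviour-specific claims are another possible reading.
- **18.5% against 5%** mixes two quantities. With two-sided tests, 18.5% includes false results against the programme. The like-for-like figures for a false favourable result are 9.6% and 2.5%. The pair 18.5% and 5% would describe false favourable results only if each test were one-sided at 0.05.

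A reader might also enlarge the family with country-specific tests. The article describes a comparison between countries, interaction effects and subgroup analyses; it does not describe separate primary efficacy tests within each country.

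These objections limit the size of the point but do not remove it. The article does choose its outcomes and time points: it names two of each and ranks none. The joint hypothesis is a sentence in the Discussion, and neither the outcome section nor the analysis section turns it into a decision rule.

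A last objection concerns T2: the planned ANCOVAs are at T3 and T4, and the hypothesis includes maintenance, which T2 cannot show. That is fair. Making T2 primary narrows the confirmatory question to the effect at the end of the programme and leaves maintenance to supportive analyses.

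**Conclusion.** The point holds in conditional form. The article fixes two unranked behaviours, two ANCOVA time points and one alpha, with no primary time point and no success rule. The programme-level error therefore depends on an unstated rule. It is at or below 5% if all four tests must succeed. It is up to 18.5% in both directions (at most 9.6% against 2.5% in favour of the programme) if any one suffices at two-sided 0.05, and lower with correlated tests. These figures rest on a family of four, two-sided testing and, for the upper values, independence. The gap should be closed before the data are seen, and doing so is cheap at the planned effect size.

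**What to change.** 1. Name one primary time point, preferably T2, because Table 1 has the waiting-list group start the intervention after it. One sentence under Study design instead places T3 beside the opening of access, so the passages on that timing must be reconciled. T2 precedes access on either reading.
2. At that time point, test physical activity and fruit and vegetable intake, adjusted for baseline, by the Holm procedure at overall two-sided 0.05. Alternatively, state that both must be significant at 0.05, which needs no adjustment. Either rule is valid; the plan has to state one.
3. Report the other time points, the country comparisons and the secondary parameters as supportive, with confidence intervals.
4. State sidedness and restate power at 0.025 for each behaviour, with the assumed dropout.

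**Cost.** A short addition to the analysis and power sections, plus a between-group ANCOVA at T2, where measurement is already planned. Holm itself adds no participants to the stated target. With 526 per arm analysed, worst-case power falls by about 0.3 of a point at d = 0.3 and by about 6 points at d = 0.2. Since the target makes no allowance for dropout, the loss at d = 0.2 would be about 8 to 10 points if 20% to 40% were lost. Much of the shortfall from 84% would then come from the dropout itself.

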### Statistical analysis

Descriptive statistics will be used to describe baseline characteristics of the study. We will assess whether there are significant differences between the intervention group in comparison with the control group according to physical activity and nutrition by means of linear regression analysis in PASW (SPSS). The pre-test and post-test measurements of the control group will be compared with the measurements of the intervention and controle group with regard to the target behaviours.

To be able to assess the impact of the intervention on the performance of physical activity and fruit and vegetable consumption, we intend to perform several analyses of covariance (ANCOVA) after four weeks (T3) and six months (T4), controlling for the baseline performance. Multivariate regression analysis will be used to determine possible confounding or modification effects. Regression analysis will allow us to identify the percentage of variability of the dependent variable that is explained by the determinants used. In order to detect differences between the study condition and the control group, effect sizes will be calculated for each study group separately [78].

Subgroup analyses will be performed to determine if the benefit of the intervention depends between groups like nationality or socioeconomic status [79]. Further, dose–response-analyses will be conducted with logistic regression to see if the intervention effect depended on the time spent on the webpage.

Baseline characteristics of participants who dropped out will be compared with participants who finished the intervention to examine whether drop out is at random or determined by specific characteristics.

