### Study design

This multinational and multicenter longitudinal study has a quasi-experimental randomized controlled trial design. The study consists of one intervention group (IG) and one waiting list control group. The intervention group will first address physical activity then fruit and vegetable consumption. The waiting list control group will get access to the intervention after the study condition has finished the intervention (T3). The waiting list control group has to complete the baseline questionnaire (T1) at the same time as the intervention group and will have access to the intervention only after their second measurement. In total, six data collection time points are planned where T0 is intended for the collection of contact information only. Baseline measurement will take place at T1 before the intervention starts, followed by a measurement (T2) after completion of the intervention. Further follow-up measurements are planned to take place after four weeks (T3), after six months (T4) and after 12 months (T5) (see Table 1).

**Table 1 T1:** Design of measurement points

**Time point**	**Measurement**
T0	Patients within cardiac rehabilitation will be asked if they are interested in participation of an aftercare program. Contact data will be collected

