	**End of the intervention period**
	**Waiting list control group starts intervention**
T3	4 week follow-up measurement
T4	6 month follow-up measurement
T5	12 month follow-up measurements

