### Randomization

During the rehabilitation period, patients will be recruited within the rehabilitation center by their therapists. These therapists will first inform the person undergoing rehabilitation about the study and hand out study information. Participants will log in on the project website and have to give online informed consent. Randomization will be done by the computer software *TailorBuilder*, which is developed for internet based tailored interventions. Participants will be randomly allocated to the study group or to the waiting list control group. The waiting list control group will get access to the intervention after eight weeks (see Table 1).

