## Discussion

The results of this study are important for the future development of online-based rehabilitation aftercare programs for cardiovascular patients and the development of online interventions in general. Although there is no doubt about the positive effect of adequate physical activity and fruit and vegetable consumption for people undergoing rehabilitation [8,11,13,17,22,80], many patients fail to maintain lifestyle changes [26-28]. To transfer the rehabilitation results into the daily life and to overcome unhealthy habits, effective rehabilitation aftercare is necessary.

Given the benefit of tailored health behavior change interventions, there is still a need for further research. It is important to develop guidelines for interventions which are effective in different countries with different rehabilitation systems. In order to make a positive contribution, an international implementation and evaluation of this study will be done within Germany and the Netherlands.

It will be assessed to what extent the health status, quality of life and return to the labor market can be realized among the participants. Our hypothesis is that participants in the intervention group will increase their level of physical activity, fruit and vegetable consumption and are able to maintain these behaviors over a longer period of time compared to the control group.

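### The only effect analyses with named time points are ANCOVAs at T3 and T4: T4 has no untreated control, T3 depends on an unreconciled access time, and T2 is not named

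*Protocol article*

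**What the plan says.** The Main study outcomes section makes physical activity and fruit and vegetable intake the primary parameters, compared between the two arms. For the programme's effect on these behaviours the Statistical analysis section states: "we intend to perform several analyses of covariance (ANCOVA) after four weeks (T3) and six months (T4), controlling for the baseline performance". The same section also plans a between-group linear regression and a pre-test/post-test comparison. Neither is given a time point, and T2 does not appear in the section.

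The article describes control access in four places:

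- Table 1 has the row "Waiting list control group starts intervention" between T2 and T3.
- Randomization: "The waiting list control group will get access to the intervention after eight weeks".
- Study design, one sentence: controls "will have access to the intervention only after their second measurement". T0 collects contact data only, so the second measurement is T2.
- Study design, another sentence: access comes once the intervention arm has finished, with T3 given in brackets. Table 1 puts that finish at T2.

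The Discussion expects intervention participants to improve and says that they "are able to maintain these behaviors over a longer period of time compared to the control group".

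**The concern.** A waiting-list design gives a randomised comparison of programme with no programme only until the controls get the programme. After that, the contrast between arms estimates early against delayed access. The only effect analyses that the article ties to time points are at T3 and T4, which lie at or beyond that boundary, while T2 is measured before controls have access on any reading and has no named analysis.

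If the programme works and controls gain from it, the later contrast shrinks, usually toward zero. This is a bias in the estimate, so a larger sample does not cure it. The claim of longer-term maintenance relative to control is affected most, because it rests wholly on the later time points.

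**Working it through.** **Timeline, in weeks from T1.** T2 is at week 8 (Table 1). T3 is four weeks later, at week 12. T4 at six months is about week 26 if counted from T1, or about week 34 if counted from T2. The programme has eight sessions, one per week. Table 2 puts physical activity in Sessions 1–4 and fruit and vegetables in Sessions 5–8. I assume that controls follow the same order and pace.

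| | Access at T2 (week 8) | Access at T3 (week 12) |
|---|---|---|
| Controls could finish | 8 + 8 = week 16 | 12 + 8 = week 20 |
| Sessions offered to controls by T2 | 0 of 8 | 0 of 8 |
| By T3, physical activity | 4 of 4 | 0 of 4 |
| By T3, fruit and vegetables | 0 of 4 | 0 of 4 |
| By T4 (week 26 at the earliest) | 8 of 8 | 8 of 8 |

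T2 is clean and T4 is after crossover in both columns. T3 differs by column and by behaviour. The zero for fruit and vegetables at T3 under T2 access needs one qualification: the Intervention text says that first-session feedback covers both behaviours, so some early exposure is possible.

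**The plan's own figure.** The inputs are "The calculation was based on an effect size of 0.3" and "with a power (1-β) of 0.8 and alpha of 0.05", with the result that "263 people have to participate in every group in each country". I take 0.3 as a standardised mean difference and the test as two-sided; the article states neither. Then

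n per group = 2(1.96 + 0.84)² / 0.3² ≈ 175,

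so 263 is not reproduced. A 2×2 interaction contrast of 0.3 would need 4(1.96 + 0.84)² / 0.3² ≈ 349 per cell, which is not 263 either. The total is consistent: 4 × 263 = 1052. The timing point does not depend on how 263 was reached; I use it below only as the stated sample size, which gives 2 × 263 = 526 per arm pooled.

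**Illustration of dilution.** Let s be the share of the effect that controls have already gained. The expected contrast is d = 0.30 × (1 − s), and power ≈ Φ(d√(n/2) − 1.96).

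| s (assumed) | d | Power, 526 per arm | Power, 263 per group |
|---|---|---|---|
| 0 | 0.300 | 0.998 | 0.93 |
| 0.25 | 0.225 | 0.95 | 0.73 |
| 0.50 | 0.150 | 0.68 | 0.40 |
| 0.75 | 0.075 | 0.23 | 0.14 |
| 1 | 0 | 0.05 | 0.05 |

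Worked case, s = 0.50. Pooled: 0.15 × √263 − 1.96 = 2.43 − 1.96 = 0.47, and Φ(0.47) ≈ 0.68. One country: 0.15 × √131.5 − 1.96 = 1.72 − 1.96 = −0.24, and Φ(−0.24) ≈ 0.40.

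The documents give no value for s, and the table allows for no dropout.

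**The case against.** A reader might infer that the main test compares treated with treated throughout, and that T2 is the only clean comparison. The documents do not support that reading.

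- No analysis is labelled primary or main. The untimed linear regression and pre/post comparison could well be the T2 test: T2 is the natural post-test, and a regression on group with baseline as covariate is the same model as ANCOVA. An article may leave that detail to the analysis plan. What stands is that T2 is not named while T3 and T4 are.
- At T3 the fruit and vegetable sessions have not reached controls under either reading, so treated versus treated does not describe that comparison.
- One Study design sentence puts control access at T3, which would leave T3 clean for both behaviours. Three statements point to T2, but the contradiction is for the authors to resolve.
- Exposure is inferred. Participants are invited weekly and need not attend, and the order of behaviours is stated for the intervention arm only. Controls will have been offered sessions, not necessarily have done them.
- It would also be too strong to say that an effective programme must look ineffective. At 25% catch-up, pooled power is still 95%. That controls might come out ahead on physical activity at T3 is conjecture.

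None of this rescues T4. Controls could have completed the programme by then under every reading.

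**Conclusion.** The concern holds in a limited form. At T4, and equally at T5, the arms differ in when they were offered the programme, not in whether they were. The T4 ANCOVA therefore does not estimate programme versus no programme, and the Discussion's maintenance hypothesis has no untreated control behind it. This follows from the article's own schedule and needs no assumption about effect size. At T3 the problem affects physical activity if access opens at T2; fruit and vegetables are largely unexposed there, and nothing is exposed if access opens at T3.

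The size of the distortion is unknown. The loss of power from over 99% to 68% (pooled) or from 93% to about 40% (one country) assumes a true effect of 0.30 SD, no dropout and controls gaining half of it. It is an illustration, not a forecast.

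**What to change.** 1. Reconcile the statements on when controls get access: T2 (week 8) or T3. The status of T3 depends on this.
2. Name the baseline-adjusted between-group ANCOVA at T2, analysed by randomised group, as the primary test for both behaviours. State the time points of the linear regression and of the pre/post comparison.
3. Label the comparisons at T4 and T5 as early versus delayed access. Do the same at T3 wherever controls already have access, physical activity in particular.
4. Reword the maintenance hypothesis in the Discussion to match.

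T2 is already planned in both arms, so the cost is mainly wording. There are two drawbacks. The controlled claim is limited to about 8 weeks. Also, Table 2 places the T2 questionnaire in Session 8, so T2 data in the intervention arm may depend on reaching the last session; the plan should say how T2 is obtained from participants who stop earlier.
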